## Method

### Trial design

The “Active 1 + FUN” intervention will be evaluated using a randomized controlled trial. The trial was registered at ANZCTR (Id: ACTRN12618001524280) on 11 September 2018. The primary outcome will be objectively measured physical activity from children. A flow diagram of randomized controlled protocol is shown in Fig. 1.

**Fig. 1 Fig1:**
[figure not shown]
Flow diagram of the cluster randomized controlled trial

### Sample size calculation

A power calculation was conducted to estimate the required sample size. Power calculation was based on the primary outcome of children’s MVPA, at the primary time point of 6-months. Calculations were conducted using G*Power 3.1.7. Based on the Healthy Dads, Healthy Kids study [29], intervention effect size was estimated at *d* = 0.5. With a Type I error probability of 0.05 and power of 0.8, the required sample size was calculated to be *N* = 128. To account for an estimated accelerometer non-compliance rate of 30% (i.e., cases with insufficient wear time) and a potential drop-out rate of 10% [14], a minimum of *N* = 204 children will be recruited.

### Participants

Students and their parents from Primary 3 to 5 (approximately 8 to 11 years old) will be recruited to take part in this study. A pool of gender-balanced participants will be recruited via eight local schools that meet our eligibility criteria. Specifically, schools will be eligible if they are (i) co-educational (i.e. mixed-sex); and (ii) either government primary schools or aided primary schools (i.e., schools that do not have an abundance of resources). We will aim to recruit at least one school from the three main regions in Hong Kong (i.e., Hong Kong Island, Kowloon or the New Territories) respectively. Invitation letters will be sent to randomly selected primary schools which meet the eligibility criteria. Before confirming their participation in the study, the Parent-Teacher Association (PTA) or school representatives will be invited to attend a briefing session to outline the background of the study. After confirmation of their participation, Primary 3 to 5 children and their parents will be recruited from schools. Approximately 25 to 30 families will be recruited from each school. Measurements of all outcomes will only be taken from participants who agree to participate in this study.

### Ethics, consent and permissions

Students and their parents will be required to provide written consent and complete the Physical Activity Readiness Questionnaire [39] to ensure they are physically healthy (i.e., no known episode of chest pain, dizziness, or joint problems after physical activity) to engage in MVPA before participating in this study. Parents will be required to sign informed consent forms if they agree to participate as a family unit. Ethical approval for the study was obtained from the Joint Chinese University of Hong Kong – New Territories East Cluster Clinical Research Ethics Committee (Ref: 2017.018).

### Procedures and randomization

Measures for primary and secondary outcomes will be taken at baseline, at the end of intervention period (accelerometer measure will be taken during a period that included the day of the tenth intervention session, secondary outcomes will be taken the week immediately before the session), and post-intervention follow-up (i.e., one year after the baseline measurement) to examine long-term intervention effects. After completing baseline measures, participants will draw a sealed envelope to determine whether they will be allocated to the experimental group or the wait-list control group. In each school, half of the recruited families will be allocated to the experimental group, and the other half will be allocated in the wait-list control group (i.e., 1:1 ratio). Participants allocated to the experimental group will receive ten bi-weekly intervention sessions over approximately 6 months immediately after baseline measures are taken. Participants allocated to the control group will be asked to attend measurement sessions, but they will only receive the intervention 12 months later (i.e., after the final follow-up time point). Each family will receive a HK$100 gift voucher for each completed assessment for the child and at least one parent. Intervention sessions will take place within school premises. All intervention sessions for a particular class will be led by the same activity leaders (two per session) throughout the intervention period. To encourage participation, each family will receive a transportation subsidy of HK$40 for the interactive workshops and activity sessions that they attend.

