The intervention also includes multiple components associated with specific behavior change strategies [40], and target specific theoretical constructs (see Table 1). The main intervention period will last for approximately 6 months, the length of intervention may vary among participating schools because of the differences of their academic calendars (exam periods, public or school holidays, and school activities would be avoided during the intervention to minimize disturbances to regular school activities). Participants will attend ten biweekly 90-min intervention sessions. Each session will consist of two parts, a 30-min interactive workshop followed by a 60-min activity session. An additional booster session will be provided approximately three months after the tenth intervention session. Both fathers and mothers will be invited to the intervention sessions, and at least one parent must be present during each intervention session.

**Table 1 Tab1:** List of intervention components and associated dosage, behavior change strategies, and hypothesized mediators

Intervention components	Dose	Description	Behavior Change techniques using Michie et al.’s [40] taxonomy	Hypothesized mediators
1. Interactive workshop	Ten 30-min biweekly sessions	Storytelling will be the critical teaching strategy for the workshops. There will be different stories and themes for each of the workshop; for instance, the key concepts of SDT and the ‘SAAFE’ teaching principle, the importance and benefits of the routinizing physical activity. A strong focus will be on ways to increase parent’s need support and reduce controlling behaviors, in which the differences between supportive and controlling behaviors will be illustrated with real-life examples.	- Goals and planning - Feedback and monitoring - Social support - Shaping knowledge - Natural consequences - Repetition and substitution - Identity	- Need support/ controlling behaviors - Competence - Autonomy - Relatedness - Autonomous motivation
2. Activity session	Ten 60-min biweekly sessions	Parents and children will attend activity sessions together. Sessions include rough and tumble play, and FMS training.	- Feedback and monitoring - Social support - Shaping knowledge - Comparison of behavior - Repetition and substitution	- Need support/ controlling behaviors - Competence - Autonomy - Relatedness - Autonomous motivation

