#### Moderate-to-vigorous physical activity – Children and parents

Children’s and parents’ time spent in daily MVPA over a five-day period will be measured using ActiGraph wGT3X-BT accelerometers worn at the waist. Using the criteria developed by Evenson, Catellier, Gill, Ondrak and McMurray [46] (for children) and Freedson, Melanson, and Sirard Freedson, Melanson, and Sirard [47] (for parents), the sum of daily minutes spent in moderate and vigorous activity will be used as a measure for MVPA. One-second epochs will be used for the calculation of MVPA [48]. Cases will be considered valid if participants wore the accelerometer for at least eight hours on a minimum of three days, with at least one weekend day. Using proximity sensors in the ActiGraph devices [49], the duration of co-physical activity periods per day will also be measured. Participants will be required to wear the devices throughout their waking hours within the five-day data collection period except during any water-based activities (e.g., water sports, bathing) or occasion where they are not allowed to wear the devices (e.g., a contact sports match).

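### The 6-month accelerometer window must contain the tenth session, so class activity in one arm inflates the 6-month contrast in MVPA and co-physical activity

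*Protocol article*

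**What the plan says.** Two places in the protocol article, the end of the Background before the objectives and Procedures and randomization, say of the end-of-intervention assessment that the "accelerometer measure will be taken during a period that included the day of the tenth intervention session". The non-accelerometer outcomes are timed differently: "secondary outcomes will be taken the week immediately before the session". Sample size calculation names 6 months as the primary time point.

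Under Intervention, each session is "a 30-min interactive workshop followed by a 60-min activity session", held every two weeks, ten times. Under Activity leader training, leaders are taught to keep sessions highly active. Wait-list families receive nothing until the 12-month measurement is complete.

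The MVPA section gives the measurement rule: "time spent in daily MVPA over a five-day period will be measured using ActiGraph wGT3X-BT accelerometers worn at the waist", and "the sum of daily minutes spent in moderate and vigorous activity will be used as a measure for MVPA". On wear, "Participants will be required to wear the devices throughout their waking hours within the five-day data collection period", with exceptions only for water activities and occasions where a device is not permitted. A case is valid with "at least eight hours on a minimum of three days, with at least one weekend day". From the same devices, "the duration of co-physical activity periods per day will also be measured". No section removes the session, or its day, from any of these measures.

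**The concern.** The abstract and the Background describe the primary outcome as children's leisure-time MVPA, and the stated aim is a more active family life beyond the classes. A supervised class is delivery of the treatment. If its minutes are counted in one arm and the other arm has no class, the arms can differ at 6 months even when no family has changed what it does on any other day.

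The error runs one way, in favour of the intervention. It reaches the primary outcome and two secondary outcomes. Co-physical activity is hit most directly, because parent and child attend the class together by design, so the class itself registers as joint activity.

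**Working it through.** **1. The plan's own figures.** A two-sided two-sample t-test with d = 0.5, alpha 0.05 and power 0.80 needs 63.8, so 64 per arm, N = 128. Inflation for 30% non-compliance and 10% drop-out: 128 / (0.70 × 0.90) = 203.2, so 204. Both match the article and are not in dispute. The planned d = 0.5 and 64 evaluable children per arm are the yardsticks below.

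**2. Over-weighting of class time.** This step needs no outside figure.
- True frequency during the programme: one session per 14 days.
- Frequency in the window: one session in 5 days.
- Ratio: (1/5) / (1/14) = 14/5 = 2.8. For a child with only three valid days, one of them the session day, it is 14/3 = 4.7.

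**3. Size of the artefact at 6 months.** The article gives neither class MVPA nor an SD. Assumptions: 20–40 minutes of MVPA in the 60-minute activity part; about 4 minutes in the same clock hour for a control child; between-child SD 15–25 min/day; every child attends, wears the device and has a valid session day; no activity displaced elsewhere.

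Formula: spurious d = (class MVPA − 4) / valid days / SD.

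| Class MVPA (min) | Net (min) | Per day, 5 valid days | d, SD 25 | d, SD 20 | d, SD 15 |
|---|---|---|---|---|---|
| 20 | 16 | 3.2 | 0.13 | 0.16 | 0.21 |
| 30 | 26 | 5.2 | 0.21 | 0.26 | 0.35 |
| 40 | 36 | 7.2 | 0.13 × 36/16 = 0.29 | 0.36 | 0.48 |

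The range over five valid days is therefore d = 0.13 to 0.48. Changing one assumption at a time from the middle case (26 net minutes, SD 20, d = 0.26):
- 80% attendance: 0.8 × 5.2 = 4.16 min/day, d = 0.21.
- Half of the net minutes displaced from other activity: 2.6 min/day, d = 0.13.
- Three valid days including the session day: 26/3 = 8.7 min/day, d = 0.43.

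**4. What this does to a test.** For a plain two-group comparison at 6 months with 64 per arm, two-sided 0.05 and no true change, d = 0.26 gives about a 31% chance of significance, against a nominal 5%. That figure belongs to a 6-month contrast only.

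**5. What it does to the declared test.** Statistical methods declares an effect when B3, the Time × Group coefficient, differs from zero. The article does not say whether Time is linear or categorical.
- Categorical Time: the 6-month interaction term carries the whole artefact.
- Linear Time over 0, 6 and 12 months: with complete data, each child's slope weights the three waves in proportion to (0 − 6), (6 − 6), (12 − 6), that is −6, 0, +6. The middle wave has zero weight, so an artefact confined to 6 months does not move B3. With missing waves the cancellation is no longer exact.

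**6. The 12-month wave.** The only later contact is a booster about three months after session 10, so no session is scheduled in the 12-month window.

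**The case against.** Four counter-arguments deserve weight.

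*Leisure time may be defined to exclude the class.* The article never defines it, and the full protocol or analysis plan, which are not shown, might. But the rule the article does state sums all daily minutes, and the section on primary and secondary outcomes says only MVPA. A definition by clock hours would also still count a class held outside lessons. That the minutes are counted is the plain reading of the text, not a certainty.

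*The class is part of the programme, so it should count.* If total activity including delivery were the target, counting it would be defensible in principle. The 2.8-fold over-weighting would remain.

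*The size rests on assumptions.* This stands. Class MVPA, attendance, wear, displacement and SD are all unknown, and the activity part includes skill practice, so it is not continuous MVPA. Three valid days for every child is an extreme case, not a central one.

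*The test may not see it.* This also stands in part. A reader might infer that the trial's declared test has a false-positive rate near 31%, or worse with fewer valid days. The article does not support that: such figures come from a t-test at 6 months, and with linear Time B3 would be largely insensitive. Nor does the problem reach the 12-month result, so sustained change is still assessed without a class in the window.

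**Conclusion.** The concern holds for the 6-month assessment. The article fixes a wear period that contains a class attended by one arm only, states a sum of all daily minutes as the measure, and gives no exclusion. Any 6-month group contrast in children's MVPA, parents' MVPA or co-physical activity is biased towards the intervention.

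The direction and the 2.8-fold over-weighting follow from the article's own schedule. The magnitude for children's MVPA, about d = 0.13–0.48 against the planned 0.5, depends on the assumptions listed: it is smaller with incomplete attendance or displaced activity and larger with fewer valid days. Whether B3 is affected depends on how Time is coded. It would be a mistake to conclude that the trial as a whole cannot give a valid answer; the 12-month measure is not affected.

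The schedule still needs correcting, because 6 months is the time point on which the trial was sized.

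**What to change.** Place the 6-month 5-day wear period in a week without a session, on the same calendar dates for both arms within a school. The other outcomes are already taken in the week before session 10, so such a week looks feasible.

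If the period cannot move, use the time stamps to exclude the session's clock hours from MVPA and co-physical activity in both arms of the school. Exclude the hours rather than the whole day: the article does not say on which day sessions fall, and if it is a weekend, dropping the day could remove the weekend day that the validity rule requires and add to the 30% non-compliance already allowed for. MVPA including the session may be reported, but only as a measure of delivery.

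The cost is either a calendar shift that must fit school exams and holidays, or one data-processing rule with slightly less wear time. No extra participants are needed, and N = 128 and 204 do not change.

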### Intervention

A relatively bottom-up approach will be adopted in designing and customizing the content of the activity sessions with reference to the fathers’, mothers’ and children’s perceived abilities (competence), the interests and the choices of physical activities (autonomy) respectively. Specifically, pre-intervention interviews will be conducted with potential participants of the study. Parent and children (five individuals per group, respectively) focus group interviews will be conducted in schools. Interviews will explore participants’ physical activity habits (e.g., “How much time did you spend on exercise or sport activities in the past 7 days?”), perceived competence (e.g., “Are you confident in doing the exercise[s]/sport[s] you have just mentioned?”, autonomy (e.g., “Can you please name 5 exercise[s]/sport[s] you like?”) and relatedness (e.g., “Can you share with me your experience of parent-child physical activities, exercise or sport activities? How do you feel? Why?”) regarding physical activity alongside the preferred types of parent-child physical activity (e.g., “If there are parent-child physical activity sessions provided, what kinds of physical activity do you want?”). Interviews with children and parents will be conducted in a quiet room within school premises. Phone interviews will be conducted with parents who are not able to attend the focus group interview during school-hours. The feedback received through these interviews will be used to fine-tune the final intervention components and contents.

The intervention also includes multiple components associated with specific behavior change strategies [40], and target specific theoretical constructs (see Table 1). The main intervention period will last for approximately 6 months, the length of intervention may vary among participating schools because of the differences of their academic calendars (exam periods, public or school holidays, and school activities would be avoided during the intervention to minimize disturbances to regular school activities). Participants will attend ten biweekly 90-min intervention sessions. Each session will consist of two parts, a 30-min interactive workshop followed by a 60-min activity session. An additional booster session will be provided approximately three months after the tenth intervention session. Both fathers and mothers will be invited to the intervention sessions, and at least one parent must be present during each intervention session.

**Table 1 Tab1:** List of intervention components and associated dosage, behavior change strategies, and hypothesized mediators

Intervention components	Dose	Description	Behavior Change techniques using Michie et al.’s [40] taxonomy	Hypothesized mediators
1. Interactive workshop	Ten 30-min biweekly sessions	Storytelling will be the critical teaching strategy for the workshops. There will be different stories and themes for each of the workshop; for instance, the key concepts of SDT and the ‘SAAFE’ teaching principle, the importance and benefits of the routinizing physical activity. A strong focus will be on ways to increase parent’s need support and reduce controlling behaviors, in which the differences between supportive and controlling behaviors will be illustrated with real-life examples.	- Goals and planning - Feedback and monitoring - Social support - Shaping knowledge - Natural consequences - Repetition and substitution - Identity	- Need support/ controlling behaviors - Competence - Autonomy - Relatedness - Autonomous motivation
2. Activity session	Ten 60-min biweekly sessions	Parents and children will attend activity sessions together. Sessions include rough and tumble play, and FMS training.	- Feedback and monitoring - Social support - Shaping knowledge - Comparison of behavior - Repetition and substitution	- Need support/ controlling behaviors - Competence - Autonomy - Relatedness - Autonomous motivation
3. Parent-child physical activity homework	Weekly parent-child physical activity sessions outside the program (accumulate at least 30 min)	Parents and children are encouraged to plan, set goals regarding parent-child physical activities and spend at least 30 min (accumulative) per week to engage in any kind of physical activities together.	- Goals and planning - Feedback and monitoring - Social support - Repetition and substitution - Self-belief	- Competence - Autonomy
4. Activity planning consultation	Two 15-min session during intervention period	The MVPA and FMS measurement results and feedback will be sent to the participants via WhatsApp. A trained research assistant will help families identify gaps in time to fit in family activities, and overcome barriers they may have encountered.	- Goals and planning - Feedback and monitoring - Social support - Repetition and substitution - Self-belief	- Competence - Autonomy
5. Easy sports equipment	One set per family	A set of equipment including skipping rope, soft volleyball, sponge flying disc, etc.	- Antecedents - Self-belief	- Competence - Autonomy
6. Online materials	Participants can view the online resources with their gadgets any time anywhere they want.	Descriptions about the required FMS in various kinds of sports will be provided. Participants can easily make comparisons between different sports and reflect on their own strengths and weaknesses.		

Storytelling will be adopted as the fundamental teaching strategy in the interactive workshops. This strategy will help facilitate participants’ understanding of the following essential concepts: (i) tenets of SDT, (ii) benefits of routinizing physical activity, (iii) time management methods, and (iv) parenting practices. There will be different stories and themes for each of workshops, which will start with a short presentation to highlight the important message of the day. Then, each workshop will be followed by interactive activities and discussions between and within families. All video and written teaching materials for these sessions will be prepared by the research team. In line with SDT, one important goal of the workshops is to teach parents how to support their children’s basic psychological needs in various contexts and scenarios and avoid using external control. Role play activities will be embedded in workshops to enable learning and sharing in a more relaxed manner.

In the second part of the intervention sessions, parents and children will participate in physical activity together. These sessions will highlight the concepts of MVPA (i.e., huff and puff activity), FMS, motivation, and “co-physical activity”. There will be a gameplay period within the session, using innovative tools and methods, such as methods previously developed by Ha, Lonsdale, Lubans and Ng [41]. These will be followed by a skill development period using a set of easy sports equipment, including skipping rope, soft volleyball, sponge flying disc, which will be given to participants for free. The aim is to improve participants’ (children and parents) FMS proficiency. Researchers have found that these skills are important determinants of physical activity participation [11]. Hence improving such skills in children and parents may increase their future participation in physical activity beyond the intervention period. Both parents of children will be invited to take part in the intervention sessions. Specifically chosen sessions will be more tailored for mothers or fathers, respectively. The corresponding parent will be strongly encouraged to take part in these classes, even though they may be unable to attend other sessions.

Apart from the workshops and activity sessions, there will be weekly parent-child physical activity homework that will encourage participants to spend at least 30 min in total per week to engage in parent-child physical activity. Physical activity homework is an effective means to promote physical activity of students outside of school hours [42–44], as such parent-child physical activity homework will also promote the physical activity level of both parents and children. An activity logbook will be given to each family to encourage parent-child physical activity planning and to self-report and provide descriptions regarding the relevant parent-child physical activities they have done (e.g., date and time, with whom, the types of co-physical activity and duration). Also, each family will receive two 15-min consultation sessions during the intervention period. Essentially, each family will receive consultations on how to overcome barriers to engaging in physical activity as a family unit. They will receive scheduling help to identify time gaps for family activities. Families will be encouraged to begin a healthier lifestyle and will be prompted to provide reciprocal reinforcement (i.e., parents and children reinforcing each other simultaneously; [29]). Participants will be assisted to set short- and long-term goals for each family member during the consultations. A research assistant will be trained specifically to provide such consultations. Furthermore, online materials regarding the interactive workshops and FMS will be provided to all the participants. Descriptions about the required FMS in various kinds of sports will be provided. Participants can easily make comparisons between different sports and reflect on their own strengths and weaknesses. A booster session with fun physical activities will be provided to the participants approximately 3 months after the 6-month main intervention period.

